### 11.4 Handling of missing data and drop-outs

Missing data regarding the outcome parameters and the decolonization will lead to patient dropout of the study. Drop-outs will be reported in the patients & methods section of the publication, drop-out of data will be reported for a minimum of 10 years after study termination or in case of premature termination of the clinical trial. Major deviations from the protocol will be regarded as drop-outs and excluded from both, the ITT and the PP populations. The independent Data Monitoring Committee may help in case of difficult interpretations of the case among the trial investigators.

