#### 6.1.2 In case of refusal or withdrawal from the study

When a patient refuses to take part in the study, or is rejected by the investigators, his/her treatment will continue according to usual therapeutic standards and follow-ups. If a patient's withdrawals his/her consent during the study period or up to one month after the last study visit, his/her information and results will be deleted from further analyses.

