#### 8.1.2 Control Comparator

Absence of decolonization and absence of the questionnaire.

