### 8.3 Compliance with study intervention

We assess the auto-declared compliance of the patients in the intervention (decolonization) arm via questionnaires and by recuperating the empty packages of the decolonization sets.

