### 9. STUDY ASSESSMENTS

#### 9.1 Assessment of primary outcome

Judged by local wound healing (healed vs delayed wound healing according to Reference). The wound healing will be assessed visually by orthopaedic surgeons. Wound nurses and the study investigators may help in the assessment of wound problems, but in case of doubtful cases, the opinion of the treating physician will dominate the decision upon the presence or absence of wound problems and/or infection.

Persistent postsurgical pain, serum laboratory markers, or the patient's subjective wound feelings will not serve as objective criteria for wound healing (or in the contrary, wound discharge and dehiscence). A wound problem solely due to stitches and localized suture problems will not count as a wound problem. A keloid or altered pigment features will not be counted as a problem in this trial. Remission is defined as the absence of any problems and as the absence of any clinical signs of infection.

The primary outcome will be assessed on both, the Intention-to-treat and the per-protocol populations.

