#### 11.3.2 Final analyses

The intent-to-treat (ITT) population will consist of all randomized patients. Patients will be analysed according to treatment group assignment. Patient disposition and baseline characteristics will be based on the ITT population.

The per-protocol (PP) population will consist of all randomized patients who complete the study (or who are otherwise defined as a treatment failure) according to the clinical investigation plan and who have not deviated significantly from the protocol. All efficacy analyses will be repeated using the PP population. Any analysis involving microbiological assessments will exclude patients without an assigned baseline pathogen.

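### Section 11.4 excludes major protocol deviators from the ITT population that 11.3.2 defines as all randomised patients, so no analysis of every randomised episode remains

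*Protocol*

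**What the plan says.** Protocol 11.3.2 opens with a conventional definition: "The intent-to-treat (ITT) population will consist of all randomized patients", analysed by assigned group. PP is the restricted set, limited to those who complete the study (or count as treatment failures) and "who have not deviated significantly from the protocol".

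Section 11.4 then states: "Major deviations from the protocol will be regarded as drop-outs and excluded from both, the ITT and the PP populations". It also says: "Missing data regarding the outcome parameters and the decolonization will lead to patient dropout of the study". No other handling of drop-outs in the analysis is given there.

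Section 9.1 fixes the analysis sets for the main result: "The primary outcome will be assessed on both, the Intention-to-treat and the per-protocol populations".

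On adherence, section 8.3 says "We assess the auto-declared compliance of the patients in the intervention (decolonization) arm via questionnaires", together with collection of the empty packages. Section 8.1.2 defines the control as "Absence of decolonization and absence of the questionnaire".

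**The concern.** The value of ITT in a superiority trial is that the groups compared are the groups randomised. Removing patients for what happened after allocation gives that up. Section 6.2 names randomisation as the trial's method of minimising bias, and 11.4 partly undoes it.

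Two features add to the worry. First, a failure to wash, an unreturned set or an absent questionnaire can be recorded only in the decolonization arm, so one source of exclusion has no counterpart among controls. Second, the trial is open. Under 9.1 the treating physician's opinion settles doubtful outcomes, and under 7.4 investigators may exclude patients who do not follow study procedures. An exclusion could therefore be decided with arm and outcome known.

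At stake is whether a positive result reflects decolonization or the selection of who stayed in the analysis.

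**Working it through.** **1. The texts side by side.** 11.3.2 puts every randomised patient in ITT. 11.4 takes major deviators out of ITT. 9.1 offers only ITT and PP for the primary outcome, and PP already omits significant deviators. If 11.4 is followed, no planned analysis contains all randomised episodes.

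**2. Missing data.** 11.4 makes missing outcome or decolonization data a cause of drop-out. Its next use of that word treats drop-outs as the class excluded from both sets. That missing-data patients also leave ITT is an inference from this, not a statement in the text.

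**3. The plan's sample size.** Inputs from 11.2 and 11.3: event risks 10% and 5%, power 80%, two-sided 5%, 1:1.

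Uncorrected n = [1.96·√(2·0.075·0.925) + 0.8416·√(0.10·0.90 + 0.05·0.95)]² / 0.05² = 434.4, so 435 per arm. With the continuity correction, (434.4/4)·[1 + √(1 + 4/(434.4·0.05))]² = 473.6, so 474. The stated 474 is reproduced, and this point does not affect it.

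**4. Bias when there is no true effect.** From the plan: 10% risk in both arms and 500 per arm. Assumed: a fraction f of the decolonization arm is excluded, no controls are excluded, and the excluded patients' risk is RR times that of the retained.

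- Retained risk: r = 0.10 / (1 − f + f·RR).
- Spurious difference: d = 0.10 − r, with 500 controls against 500(1 − f).
- Chance of a false benefit claim: 1 − Φ[(1.96·SE₀ − d)/SE₁], where SE₀ is pooled and SE₁ unpooled.

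Worked case, f = 0.10, RR = 2: r = 0.10/1.10 = 0.0909 and d = 0.0091. The pooled risk is (50 + 40.9)/950 = 0.0957, giving SE₀ = 0.0191 and SE₁ = 0.0191. The result is 6.8%.

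| RR | False benefit, f = 10% | False benefit, f = 20% |
|---|---|---|
| 0.5 | 1.3% | 0.6% |
| 1 | 2.5% | 2.5% |
| 1.5 | 4.3% | 6.6% |
| 2 | 6.8% | 13% |
| 3 | 14% | 32% |

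The nominal value is 2.5%. At RR = 1 there is no bias; at RR = 0.5 it reverses.

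**5. If decolonization works but some do not adhere.** Assume non-adherers keep the 10% risk. The true ITT risk in the decolonization arm is 0.05(1 − f) + 0.10f, which is 5.5% at f = 10% and 6.0% at f = 20%. The ITT difference is then 4.5 or 4.0 points, whereas excluding non-adherers would report 5.0.

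Power at 500 per arm (normal approximation, no continuity correction) is 85.2% with full adherence, 75.9% at f = 10% and 64.5% at f = 20%. Restoring 80% power, with the continuity correction used for the 474, would take 597 or 771 per arm.

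**The case against.** The strongest reply accepts the contradiction and disputes what is built on it. Several of its points stand.

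- **Direction.** A reader might infer that 11.4 favours decolonization. The documents do not establish this, since nothing in them links poor adherence to a higher infection risk. The table shows no bias at equal risk and a reversal at lower risk. Section 9.2.5, which ends participation early for patients needing antibiotics beyond end of treatment, could remove events from either arm, including the control arm.
- **One-sidedness.** A reader might infer that only decolonization patients can be excluded. The rule covers all major deviations; eligibility breaches or use of other antiseptics can occur among controls, as can missing outcomes. Uneven is supportable, one-sided is not.
- **Scale.** Incomplete washing is nowhere classed as a major deviation, and the 10% and 20% fractions are assumptions. Section 9.2.3 expects few drop-outs; the transfers and non-infectious deaths it mentions are given as very exceptional situations.
- **Mitigation.** Section 7.4 allows treatment to stop while follow-up continues, 8.4 asks withdrawn participants to continue surveillance, and 11.4 lets the independent committee help with difficult cases. These may limit missing outcomes, but they do not return an excluded deviator to ITT.

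Section 6.1.2, under which a withdrawing patient's data are removed ("his/her information and results will be deleted from further analyses"), might be read as part of the same defect. It is a separate consent matter that applies to both arms, and this point does not rest on it.

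**Conclusion.** Wrong as written. The conflict between 11.3.2 and 11.4 over deviators is literal, and nothing elsewhere in the protocol resolves it. Because 9.1 relies on ITT and PP alone, the primary superiority comparison would not rest on the groups as randomised. This is not detail deferred to an analysis plan: the protocol itself fixes the rule.

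The supported claim stops there. Removal of missing-data patients from ITT is a strong inference. Bias may run either way; towards decolonization is the likelier concern, either because the excluded patients may be at higher risk or because non-adherence would dilute a real effect. The illustrative range for a false benefit claim, 0.6% to 32% against a nominal 2.5%, depends wholly on assumed exclusion fractions and risk ratios and on no exclusions from the control arm. It would be too strong to say that the result is certain to be materially distorted, since the distortion scales with the number excluded, which is unknown.

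**What to change.** - Delete the exclusion from ITT in 11.4, and confine deviation exclusions to PP.
- Keep the 11.3.2 definition as the only one: every randomised episode, analysed as assigned, whatever the adherence, deviation or completeness of decolonization data.
- State that episodes with incomplete follow-up stay in ITT, censored at last contact in the Cox model already planned in 11.3.
- Name ITT as the analysis that decides superiority, with PP as supportive.

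The change itself is wording only and leaves the 474 per arm as it is for its own inputs. The cost in effect size and power may be more than slight: if some decolonization patients do not adhere, the dilution shown in step 5 of the working becomes visible in the main result. The sponsor should decide knowingly whether 500 per arm still suffices under the non-adherence it expects.

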## 12. QUALITY ASSURANCE AND CONTROL

The Sponsor-Investigator will implement and maintain quality assurance and quality control systems with written SOPs and Working Instructions to ensure that the clinical investigation is conducted, and data are generated, documented (record), and reported in compliance with the clinical investigation plan, GCP, and applicable regulatory requirement(s). Monitoring and audits will be conducted during the study for quality assurance purposes.

### 12.1 Data handling and record keeping / archiving

Data is exclusively stored using the secured REDCap® electronic data capture tool. The PI is responsible for collection of data and possesses the screening log, where confidentiality is ensured by using participants' ID. Study IDs are distributed by REDCap® automatically in ascending order. Access authorization via Log-in (User) and password will be given by the PI to people on the staff list (people involved in the study), as necessary. For this reason, data cannot be changed by non-authorized people. REDCap® documents every relevant processing step to ensure traceability with registration software and is secured daily via backups. All transaction logs between performing of two backups will be secured for one week while every study data in REDCap® will be secured for an unconfined time, at least for 10 years. Its data base server is allocated in highly modern rooms in Rümlang ZH and Altstetten ZH with protection of access. Collected data of this study is visible for inspection of independent ethic committee and authorities.

When the study is terminated, data will be stored in the same system. Data can only be accessed by defined persons that have contributed to the project. Source Data are going to be stored in the institutions PACS and KISIM system according to the institutional standard at the Balgrist.

### 12.1.1 Case Report Forms

Electronic case report forms (eCRF) will be used, one for each enrolled study participant, to be filled in with all relevant data pertaining to the participant during the study. All participants who either completed the screening successfully or were considered not-eligible or were eligible but not enrolled into the study have to be documented on a screening log. The participation of each study participant will be documented on the Enrolment Log. For data and query management, monitoring, reporting and coding an internet-based secure data base REDCap® developed in agreement to the Good Clinical Practice (GCP) guidelines will be used. It is the responsibility of the PI to assure that all data in the course of the study will be entered completely and correctly in the respective data base. Corrections in the eCRF may only be done by the investigator or by other authorized persons. In case of corrections the original data entries will be archived in the system and can be made visible. For all data entries and corrections date, time of day and person who is performing the entries will be generated automatically. Documented medical histories and narrative statements relative to the participant's progress during the study will be maintained. These records will also include the following: originals or copies of laboratory and other medical test results (e.g. ECGs, etc.) which must be kept on file with the individual participant's eCRF. The investigators perform a complete and accurate documentation of the participant data in the eCRF.

### 12.1.2 Specification of source documents

Source data will be available at the site to document the existence of the study participants and substantiate the integrity of study data collected. Source data will include the documents relating to the study, as well as the medical treatment and medical history of the participant.

The following information (at least but not limited to) will be included in the source documents:

- Demographic data (age, sex).
- Inclusion and Exclusion Criteria details.
- Participation in study and signed and dated Informed Consent Forms.
- Visit dates.
- Medical history and physical examination details.
- Key efficacy and safety data (as specified in the protocol).
- SAEs, AEs and concomitant medication.
- Results of relevant examinations.
- Laboratory printouts.
- Reason for premature discontinuation.
- Randomization number.

Source data will always be kept with the regular patient file.

The following documents are also considered source data, including but not limited to:

- SAE worksheets.
- Nurse records, records of clinical coordinators.
- Medical records from other department(s), or other hospital(s), or discharge letters and correspondence with other departments/hospitals, if participant visited any during the study period and the post study period.

### 12.1.3 Record keeping / archiving

All study data must be archived for a minimum of 10 years after study termination or premature termination of the clinical trial. Data are stored using the proprietary hospital information system and REDCap electronic data capture tool hosted at the Balgrist.

## 12.2 Data Management System, access and back-up

Subject-related data will be stored in the research electronic data capture software REDCap. Back up will be kept on a hard drive belonging to the PI and later on stored in the archives of the UKB, as mentioned above. The PI and the co-investigators are responsible for data recording. The PI will grant the relevant personnel user rights to view and/or edit data entries by password as applicable. All edits will be automatically documented in the change history log.

### 12.2.1 Analysis and archiving

For data analysis, subject-related data from REDCap will be exported and analyzed in statistics software (IBM – SPSS and/or STATA, Version 14, College Station, USA). Before data export, all patient identifiers will be removed. All eCRF data will be stored for a minimum of 20 years.

## 12.3 Monitoring

Regular monitoring visits at the investigator's site prior to the start, during the interim analysis and at the end of the study, will help to follow up the progress of the clinical study, to assure utmost accuracy of the data and to detect possible errors at an early time point. The Sponsor-Investigator organizes professional independent monitoring for the study.

All original data including all patient files, progress notes and copies of laboratory and medical test results must be available for monitoring. The monitor will review all or a part of the eCRFs and written informed consents. The accuracy of the data will be verified by reviewing the above referenced documents.

One monitoring visit at the investigator's site prior to the start and twice during the course of the study will be organised by the Sponsor-Investigator. Furthermore, there will be a close-out visit at the study end. During the monitoring, all documents including source data/documents will be accessible for the monitor and all questions will be answered.

| Study period | Time                          | Monitoring                                                                                                                                                                                                                                                                                                                                                               |
|--------------|-------------------------------|--------------------------------------------------------------------------------------------------------------------------------------------------------------------------------------------------------------------------------------------------------------------------------------------------------------------------------------------------------------------------|
| Before study | January or February 2023      | Monitoring will be informed about study conduct concerning data sampling and safety reporting.
Monitor controls if 
 
Documents are approved
 
Documents are at site
 
Investigators are familiar with study protocol and safety reporting
 
Investigators know their duties and responsibilities
 
 |
| During Study | Spring 2024                   | All subjects: SDV for existence and informed consent
First trial participant and at least 10% of trial participants recruited at the time of the monitoring visit, as far as available: eligibility, primary endpoint, SAEs                                                                                                                                           |
| Study end    | December 2024
January 2025 | Control for completeness of source data                                                                                                                                                                                                                                                                                                                                  |

## 12.4 Audits and Inspections

A quality assurance audit/inspection of this study may be conducted by the competent authority or CEC, respectively. The quality assurance auditor/inspector will have access to all medical records, the investigator's study related files and correspondence, and the informed consent documentation that is relevant to this clinical study. The investigator will allow the persons being responsible for the audit or

the inspection to have access to the source data/ documents and to answer any questions arising. All involved parties will keep the patient data strictly confidential.

## 12.5 Confidentiality, Data Protection

Direct access to source data may be granted in the case of monitoring, audit or inspections. All personnel must treat patient data as confidential. As far as possible, encoded data will be used. Only persons listed on the staff list have access to the source data.

## 12.6 Storage of biological material and related health data

All health-related patient data will be stored and archived in the data capture software REDCap. Patient-source data will be registered using subject identifiers. After full data analysis, all subject identifiers will be erased. Patient-source data may still be saved in the patient's medical record. Collection, disclosure, storage of patient-related data is carried out in accordance with Swiss data protection regulations and the Human Research Act. A requirement is the informed consent of every subject prior to inclusion in the clinical trial.

## 13. PUBLICATION AND DISSEMINATION POLICY

After the statistical analysis of this trial, the sponsor-investigator will make every endeavour to publish the data in (a) medical journal(s), to be able to communicate the results to healthcare professionals, the public and other relevant groups. All participants will be sent a free copy of the published article. There will not be any publication restriction and we plan to sort at least three major publications. We will also present preliminary results in national, regional, and international scientific meetings.

All investigators indicated in this protocol, and eventually additional colleagues participating in the future, will be co-authors of this study according to their individual contributions. The main study nurse, all Sponsors and Principal Investigators will participate in all publications. In selected publications, members of the corresponding orthopaedic teams will participate as co-authors and depending on their investment into the study.

## 14. FUNDING, BUDGET AND SUPPORT

The global (undetailed) Budget is planned as follows (all currencies in Swiss Francs CHF):

| Costs                     | Total         | 1 st Year | 2 nd Year |
|---------------------------|---------------|----------------------|----------------------|
| a. Ethical Committee      | 3,000         | 3,000                | 0                    |
| b. Monitoring             | 5,000         | 2,500                | 2,500                |
| c. Nurse 20% for 2 years  | 39,000        | 19,500               | 19,500               |
| d. Social securities      | 5,654         | 2,827                | 2,827                |
| e. Miscellaneous          | 2,346         | 423                  | 1,923                |
| Swiss Francs (CHF) | 55,000 | 28,250        | 26,750        |

Schülke & Mayr AG, [name], Schweiz will support the study with an unconditional donation of 55,000.- (fifty-five thousand) Swiss Francs (paid in two tranches), which will be used for the salary of the study / infection control nurses, the Monitoring and for the Ethical Committee fees. The study team will not make financial profit and cover the minimal operational costs.

Schülke & Mayr GmbH will also grant/donate all the decolonization kits used for the study, for free (including the corresponding transport costs).

Schülke & Mayr GmbH has the rights to consult the data and the draft, but will not be part of the study / academic team that will publish the results of the BALGDEC study.

